### Quantitative Study Population

This study’s cohort will include patients who receive care for SUD. Eligible patients are adults aged 18 years and older with an incident SUD identified between January 1, 2017, and May 31, 2025. We will include both group practice enrollees, who receive most of their care from internal KPWA-owned and operated clinics, and KPWA health insurance plan enrollees who primarily receive care outside the internal delivery system (IDS). Incident SUD is defined as meeting any of the following criteria at a clinical encounter with no prior SUD indicators in the past 6 months: (1) a newly documented SUD diagnosis, or (2) two or more *DSM-5* (*Diagnostic and Statistical Manual of Mental Disorders, Fifth Edition*) symptoms reported on standardized patient symptom checklists. The index date will be the date of the qualifying incident SUD event. The 6-month “washout period” is used to define new treatment, modeled on National Committee on Quality Assurance definitions [36], but we may explore the sensitivity of sample definitions using other time frames, such as 60 days [37]. For patients who have been enrolled in KPWA for less than the length of the washout period, we will consider their first SUD event to be an incident SUD event. Provisionally, multiple qualifying incident SUD events from the same patient will be included in the analysis (see details in Statistical Analyses). Patients will be excluded from the analyses if they have opted out of research participation with the health plan (≈0.2%).

The analytic sample will be split into distinct study subcohorts comprising patients with incident SUD identified in the specific clinical settings. We anticipate using five subcohorts, including: (1) primary care, (2) urgent care, (3) ED or hospital, (4) behavioral health, and (5) all other settings. These locations are identified based on EHR and insurance claims data that code clinic departments, places of service, encounter types, and SUD diagnosis data available in each location (Table 1). Once patients are identified as having an incident SUD and meeting the inclusion criteria described above, they enter the initial state of the MSM.

**Table 1. T1:** Study subcohorts defined by the clinical setting in which an incident substance use disorder event occurs. Incident SUD^a^ events are identified for adult patients aged 18 years and older and are categorized into 1 of the 5 subcohorts in this table.

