Cohort	Location description	Specification of the triggering event
1	Primary care	Documentation of an SUD diagnosis OR 2+ SUD symptoms as part of follow-up assessment after a positive population-based SUD screen in specified setting
2	Urgent care	Documentation of an SUD diagnosis OR 2+ SUD symptoms as part of follow-up assessment after a positive population-based SUD screen in a specified setting
3	Behavioral health	Documentation of an SUD diagnosis OR 2+ SUD symptoms as part of follow-up assessment after a positive population-based SUD screen in a specified setting
4	All other settings	Documentation of an SUD diagnosis OR 2+ SUD symptoms as part of follow-up assessment after a positive population-based SUD screen in a specified setting
5	Emergency department or hospital	Documentation of an SUD diagnosis in the specified setting

a SUD: substance use disorder.

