### Quantitative Data Sources

Data for this study will be drawn from KPWA’s EHR, health insurance claims, membership enrollment records, and death data, as well as additional cause of death data collected from Washington State. KPWA EHR data provide comprehensive encounter-level records on all health services received by members. These data include information on all in-person and virtual encounters, including telephone visits and secure messages. This information is primarily captured through real-time utilization and clinical information abstracted from the EpicCare EHR. Data entered into the EHR are maintained in a relational database that allows linkages across individuals, encounters, and health measures. Membership enrollment records document individuals’ enrollment history, source of insurance, benefit design, demographic information, and medical bill financial assistance requests. Health care claims submitted by contract providers and facilities will be used to capture services not provided within KPWA’s IDS. For instance, all ED care is provided outside of the IDS. KPWA obtains nearly 99% complete data of externally provided services within 6 months of delivery. From Washington State, we will obtain death data containing causes and dates of death, provided that these events occur in the state of Washington [38]. The publicly available social determinants of health (SDOH) Database created by the Agency for Healthcare Research and Quality (AHRQ) will be used to ascertain socioeconomic characteristics (eg, per capita income and unemployment rate) and health care resources (eg, number of physicians and number of hospital beds) in patients’ residence county.

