#### Substance Use Data

Patient self-reported substance use frequency, patient self-reported SUD symptoms, and clinician-documented SUD diagnoses will be used to construct states. In the creation of initial states, diagnosis codes, service procedure codes, and revenue codes help determine whether a given health care visit was related to SUD. For instance, some initial states are defined by a new clinician-documented SUD diagnosis, while others are also defined to capture clinical workflows where patients are first identified as having substance use by the nature of a health screening (eg, substance use screening in primary care). Care states require an accompanying clinician-documented SUD diagnosis, unless the care state involves a procedure or medication that is solely indicated for SUD (eg, outpatient addiction treatment or disulfiram medication). The SUD remission state is captured using self-reported substance use frequency and SUD symptoms, and clinician-reported SUD remission diagnoses.

To obtain patient self-reported substance use frequency data, clinicians are prompted by the EHR to conduct annual screening with patients in primary care. During in-person visits, screenings are administered on paper or tablet by medical assistants, then entered into the EHR. In telephone or video visits, patients complete a questionnaire via an online patient portal. Validated substance use screening measures assess past-year alcohol, cannabis, and other drug use [32,39,40]. Patients with screening scores that are deemed to be at high risk for SUD are asked to complete a follow-up assessment for symptoms of SUD using the Alcohol Symptom Checklist and the Substance Use Symptom Checklist, respectively. These 11-item checklists capture symptoms of SUD that align with the 11 *DSM-5* diagnostic criteria [41]; the cutpoint of 2 or more symptoms is consistent with SUD. The checklists have demonstrated strong psychometric properties [42-44].

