**Figure 2. F2:**
[figure not shown]
Stacked plot showing the probability of occupying specific care states or terminal over time (hypothetical). This hypothetical example shows the probability of ceasing SUD care increases steadily through day 15 and then plateaus through day 30, which could suggest a need for providing interventions to maintain engagement soon after a patient’s index SUD event. Over half of patients have ceased SUD care or have achieved SUD remission by day 45. SUD: substance use disorder.

What are inefficient sequences of SUD care following each initial state over time? Several inferences from the MSM may be a signal for inefficient SUD care. First, prolonged time in some states, such as inpatient care, may reflect challenges in coordinating care with services following an inpatient stay. We will thus identify states with relatively long mean sojourn time [67]. Second, care states with a low probability of being reached, or that take a long time before they are reached, may reflect barriers to care such as long wait times. To identify these care types, we will explore states with long expected first passage times [68] and low hitting probabilities [67]. We will also construct survival plots to display how the probability of starting in an initial access point (eg, index SUD event in primary care) and not reaching a target care state changes over time. For example, Figure 3 displays the probability of not reaching a target care state (eg, behavioral treatment and counseling in an outpatient setting) from different initial states. In this example, the probability of not reaching behavioral treatment and counseling in an outpatient setting following entry into the ED cohort is markedly higher than the corresponding probabilities following entry into the primary care or MHAC cohorts, suggestive of referral inefficiencies in ED services.

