**Figure 3. F3:**
[figure not shown]
Transition-free (or survival) probability by initial access state (hypothetical). This hypothetical survival plot displays how the probability of not reaching a given state can be graphed as a function of the initial state. In this example, the probability of not reaching behavioral treatment and counseling in an outpatient setting (not shown) is markedly higher when the incident substance use disorder event occurs in the emergency department setting, when compared to primary care or behavioral health settings. Potentially, this is suggestive of inefficiencies in referring people from emergency department settings to behavioral treatment and counseling in an outpatient setting.

What is the contribution of care states in achieving terminal states? We will calculate restricted mean survival times (RMSTs) [69] between a given SUD care state and each terminal state. An example of RMST quantities between select care states and a terminal state is presented in Table 5. The RMST captures the average terminal-event-free time, which in this study reflects time before reaching a terminal state, calculated as the area under the terminal-event-free curve over a prespecified time interval since the entry to the given care state. Figure 4 presents an example of terminal-event-free curve estimates using states from Figure 1. In this example, care types that produce lower RMSTs are those more likely to end in ceasing SUD care. Identifying these care types can inform targeted efforts, such as enhancing care coordination or improving staff levels in specific settings or for patients who receive certain treatment modalities to increase retention in SUD care.

**Table 5. T5:** Restricted mean survival times (RMST) from selected care types to ceasing care.

Substance use disorder (SUD) care state	Follow-up time (days)		
	30	60	90
Behavioral treatment and counseling, outpatient	μ₁,₄(30)^a^	μ₁,₄(60)	μ₁,₄(90)
Evaluation and assessment, intensive outpatient treatment	μ₂,₄(30)	μ₂,₄(60)	μ₂,₄(90)
Pharmacotherapy, outpatient	μ₃,₄(30)	μ₃,₄(60)	μ₃,₄(90)

a 𝜇_i_,_𝑗_(𝑡_𝑜_) is the restricted mean survival times from state i to state j over time interval 𝑡_𝑜_, where i=1 (behavioral health counseling, outpatient), 2 (evaluation and management, intensive outpatient treatment), and 3 (pharmacotherapy, outpatient); j=4 (ceasing substance use disorder care).

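### Comparisons between starting settings mix route of identification with referral performance, because the ED/hospital subcohort requires a diagnosis while the other four also admit on a symptom checklist

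*Protocol article*

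**What the plan says.** **Entry.** The Quantitative Study Population section defines the incident event without restricting it by setting: "Incident SUD is defined as meeting any of the following criteria at a clinical encounter with no prior SUD indicators in the past 6 months". The criteria are a new diagnosis or two or more DSM-5 checklist symptoms. Table 1 then differs by setting. Primary care, urgent care, behavioral health and all other settings take "Documentation of an SUD diagnosis OR 2+ SUD symptoms as part of follow-up assessment after a positive population-based SUD screen". ED or hospital takes "Documentation of an SUD diagnosis in the specified setting".

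**Counting care.** The Substance Use Data section states: "Care states require an accompanying clinician-documented SUD diagnosis, unless the care state involves a procedure or medication that is solely indicated for SUD". Its examples of the exception are outpatient addiction treatment and disulfiram.

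**Where screening happens.** In the same section, "clinicians are prompted by the EHR to conduct annual screening with patients in primary care". Study Design and Setting says annual screening covers adult group practice patients. The cohort also includes plan enrollees who mainly use outside care. Quantitative Data Sources adds that "all ED care is provided outside of the IDS", so ED events come from claims.

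**Interpretation.** The Aim 2 text on inefficient sequences describes a hypothetical ED curve with a higher probability of not reaching outpatient counseling, and calls it "suggestive of referral inefficiencies in ED services". The Figure 3 legend is more guarded: "Potentially, this is suggestive of inefficiencies in referring people from emergency department settings to behavioral treatment and counseling in an outpatient setting". Table 3 uses accessibility of care states to judge whether care is reached at the expected rate.

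**Adjustment.** Separate models are fitted per subcohort. The covariates named include SUD type and severity. Trigger type (clinician diagnosis or checklist only) is not named in the Covariates section, the Aim 1 model description, the sensitivity analyses or the subgroup analyses.

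**The concern.** A patient who enters on a checklist alone has no clinician diagnosis at index. Unless a diagnosis is coded later, or the service is specific to SUD, that patient's visits do not enter a care state. Such patients can make up part of four subcohorts and, by definition, none of the ED/hospital subcohort. Their share probably also differs among the four, since systematic screening is prompted in primary care.

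Two settings that refer diagnosed patients equally well could then show different times to care, hitting probabilities and survival curves. Because the plan offers these contrasts to health systems as a guide to where referral needs work, a difference in case-finding could be taken for a difference in referral. A real ED shortfall could also be hidden.

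**Working it through.** The plan states no figure on this point, so there is none to reproduce. The definitions were compared directly, and a simple mixture calculation shows the direction and possible size.

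**Inputs, all assumed; the documents give none of them**
- *p*: probability that a diagnosed entrant reaches counted care, set equal in both settings (identical referral). Range 0.30 to 0.50.
- *f*: share of a mixed-entry subcohort that entered on the checklist alone. Range 0.10 to 0.50. In ED/hospital, *f* = 0 by Table 1.
- *r*: uptake of counted care in checklist-only entrants relative to diagnosed entrants. Range 0.25 to 0.75, with *r* = 1 as the null case.

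**Formulas**
- ED/hospital: P(reach) = *p*
- Mixed-entry subcohort: P(reach) = (1 − *f*)·*p* + *f*·*r*·*p*
- Gap from entry criteria alone = *f*·*p*·(1 − *r*)

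| *p* | *f* | *r* | Not reached, ED/hospital | Not reached, mixed entry | Gap (percentage points) |
|---|---|---|---|---|---|
| 0.30 | 0.10 | 0.75 | 0.700 | 0.7075 | 0.10 × 0.30 × 0.25 = 0.75 |
| 0.40 | 0.30 | 0.50 | 0.600 | 0.660 | 0.30 × 0.40 × 0.50 = 6.0 |
| 0.50 | 0.50 | 0.25 | 0.500 | 0.6875 | 0.50 × 0.50 × 0.75 = 18.75 |
| any | any | 1.00 | 1 − *p* | 1 − *p* | 0 |

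The first and third rows are the extremes of the assumed ranges, hence about 1 to 19 points.

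**Direction.** For *r* < 1 the mixed-entry subcohort looks worse and ED/hospital relatively better. The hypothetical Figure 3 shows the opposite pattern, so this mechanism would not by itself produce the ED deficit drawn there.

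**Masking.** Take the second row for primary care: overall reach is 0.70 × 0.40 + 0.30 × 0.20 = 0.34. If ED-diagnosed patients truly reached care at 0.34 against 0.40 for primary-care-diagnosed patients, the overall figures would be 0.34 and 0.34. A real deficit of 6 points would not be seen.

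**After the fix.** Among diagnosis-triggered entrants *f* = 0 in every setting and the gap in this calculation is 0. Differences in case mix and data source would remain.

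**The case against.** Much of the case on the other side is sound.

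- **The asymmetry has a plausible reason and is disclosed.** ED care is external and seen through claims. The Substance Use Data section says openly that some initial states rest on a diagnosis while others also capture screening workflows. This explains the design but does not make the subcohorts comparable.
- **The interpretation is hedged.** Figure 3 is hypothetical, its legend is cautious, the study is called exploratory and Limitations disclaims causal inference. This stands. However, the misclassification example in Limitations is underreporting of substance use, and readers are not warned that entry criteria differ by setting.
- **Much of the output is within-setting.** The 7-day and 30-day follow-up measure uses only patients identified in the ED and is unaffected. The point concerns between-setting contrasts only.
- **Severity is a planned covariate and the lists are illustrative.** Severity may partly track trigger type, but it is not the same as having a clinician's diagnosis at entry. A fuller covariate list may exist elsewhere, so the objection rests on the definitions and the intended reading that this article fixes.
- **Restricting to diagnosed entrants can hide a real gap.** A symptomatic patient who is never diagnosed or treated may be a true failure of that setting's pathway. This stands, and it rules out diagnosis-only restriction as the sole comparison.

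A reader might also infer that care counts only with a diagnosis, or that brief counseling after a positive checklist is recorded as no care. The first ignores the stated exception for SUD-specific services. The second cannot be settled, because the article does not say how such visits are coded or how often a diagnosis accompanies them.

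**Conclusion.** The point holds in limited form. Contrasts between starting settings, as in Figure 3 and the accessibility rows of Table 3, combine route of identification with referral performance, and the plan names nothing that separates them.

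If checklist-only entrants reach counted care less often, ED/hospital is flattered and an ED referral deficit could be masked. The size rests on two quantities the article does not report: the checklist-only share and the relative uptake. It is about 1 to 19 percentage points over the assumed ranges and zero if uptake is equal.

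A reader might go further and conclude that these contrasts reflect only how patients were found, or that settings must differ by construction. The documents do not support that. The four mixed subcohorts also admit on a diagnosis, checklist entrants may be diagnosed later, and the gap vanishes at equal uptake. Nor does the mechanism explain away an ED deficit of the kind pictured, since it works in the other direction.

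**What to change.** 1. Record trigger type at index (clinician diagnosis or checklist only) as an analysis variable.
2. Present every between-setting contrast stratified by trigger type. Use the diagnosis-triggered stratum as the like-for-like comparison with ED/hospital, and show checklist-only entrants as their own group alongside the overall estimate.
3. Read a setting difference as suggestive of referral inefficiency only if it holds in the diagnosis-triggered stratum. State that case mix and data source still differ between settings.

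**Cost.** The trigger is already needed to assign patients under Table 1, so no new data are required. Each stratum is smaller, and some transitions may fall below the Aim 1 guideline of 40 events (10 under the permissive rule). Where that happens, it should be reported. Otherwise the change is a few lines of analysis plan and slightly more output.

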### Quantitative Data Sources

Data for this study will be drawn from KPWA’s EHR, health insurance claims, membership enrollment records, and death data, as well as additional cause of death data collected from Washington State. KPWA EHR data provide comprehensive encounter-level records on all health services received by members. These data include information on all in-person and virtual encounters, including telephone visits and secure messages. This information is primarily captured through real-time utilization and clinical information abstracted from the EpicCare EHR. Data entered into the EHR are maintained in a relational database that allows linkages across individuals, encounters, and health measures. Membership enrollment records document individuals’ enrollment history, source of insurance, benefit design, demographic information, and medical bill financial assistance requests. Health care claims submitted by contract providers and facilities will be used to capture services not provided within KPWA’s IDS. For instance, all ED care is provided outside of the IDS. KPWA obtains nearly 99% complete data of externally provided services within 6 months of delivery. From Washington State, we will obtain death data containing causes and dates of death, provided that these events occur in the state of Washington [38]. The publicly available social determinants of health (SDOH) Database created by the Agency for Healthcare Research and Quality (AHRQ) will be used to ascertain socioeconomic characteristics (eg, per capita income and unemployment rate) and health care resources (eg, number of physicians and number of hospital beds) in patients’ residence county.

### MSM Setup

Data required for fitting MSMs include care occurrences and corresponding event times to characterize state occupancy and transitions over time, along with time-invariant and time-varying covariates. SUD-related medical conditions will be incorporated as covariates when they are expected to influence care type or care setting. Additional details are provided in the analysis section. The time scale for the MSMs is continuous calendar time, with time since entry into each state reset to 0 (“clock reset”) at state entry for modeling transition intensities.

### States for the MSMs

States will capture 3 types of events related to SUD care: initial states, transient states, and terminal states. Defining states requires a balance of specificity to produce actionable information, and parsimony to allow for an estimable statistical model with accurate estimates and smaller SEs.

Initial states in the MSMs represent the clinical settings that triggered an incident event at the start of an SUD care episode, corresponding to the 5 subcohorts in Table 1.

There are 3 types of transient states. The first type is care states, which include different types of care provided in the health care system to treat the SUD, defined by combinations of setting and service type (Table 2). We opted to define 15 preliminary SUD care states based on a combination of 3 settings and 5 service types. The second type of transient state is temporary discontinuation of care. Entry into the temporary discontinuation care state is triggered using a clinically meaningful threshold for time elapsed between SUD treatment visits. The last transient state is SUD remission, which represents an improvement in the patients’ disease.

**Table 2. T2:** Transient states and terminal states are represented in the multistate models.

Category	States included	Description
Transient states	A total of 17 transient states include 15 care states derived from crossing 5 service types with 3 care settings; temporary discontinuation of SUD^a^ care; and remission of use disorder.	Care states Service types Evaluation and assessment Behavioral treatment and counseling Prevention, education, and case management Pharmacotherapy Other service Settings Outpatient Intensive outpatient Inpatient or residential Other transient states Discontinuation of SUD care A lack of SUD care over a specified period^b^ Remission of use disorder Low risk score on alcohol and substance use screen; clinically meaningful reduction on screening scores or <2 symptoms on *DSM-5*^c^ checklist; SUD remission diagnosis
Terminal states	4 states representing the end of a care episode	Death, derived from dates in health care enrollment records or Washington State death data Loss to follow-up, defined as at least 31 days without KPWA insurance coverages Ceased SUD care (no medication fills or services with a qualifying SUD diagnosis for more than 194 days Administrative censoring (in the middle of a care episode when data collection ends)

a SUD: substance use disorder.

b Temporary discontinuation will be defined separately for each care state using an appropriate threshold for time elapsed between visits that reflects acceptable gaps in care for that specific state. All of these periods will be shorter than 194 days to distinguish temporary discontinuation from ceasing substance use disorder care.

c *DSM-5*: *Diagnostic and Statistical Manual of Mental Disorders, Fifth Edition*.

Terminal states indicate the end of an SUD care episode (Table 2), such as ceasing SUD care.

